**Fig. 1 Fig1:**
[figure not shown]
Schematic overview of the CHAMPS study

### Clinic selection and patient eligibility

Three HIV community clinics for this study were selected due to agreement to participate in the study, granted study access to electronic medical records, and willingness to make office changes to increase vaccination rates. Patients will be recruited from these three clinics and enrolled in the study based on the following eligibility criteria: 1) HIV positive; 2) 18–45 years of age; 3) understand English; 4) capable of informed consent; 5) have not received or completed the three dose HPV vaccine; 6) no contraindications to receiving the HPV vaccine (i.e., history of an anaphylactic allergy to latex, an immediate hypersensitivity to yeast, current moderate or severe acute illness, and/or are currently pregnant).

### Pre-implementation approach

During the pre-intervention phase of the trial, each clinic site enrolls patients who receive immunizations using the GRITS system. The GRITS system offers a variety of functions for health care providers including recording immunizations, validating immunization history, providing immunization recommendations, producing recall and reminder notices, generating vaccine usage and client reports, and performing data extraction. Clinics will register with the 4 Pillars™ Program and clinic staff will complete a pre-intervention survey that assesses readiness and confidence in increasing HPV vaccination and current vaccination practices. Providers and clinic staff will be asked to participate in a focus group for feedback on tailoring the intervention for their clinic population prior to program implementation.

### Clinic-level intervention approach

The 4 Pillars™ Program offers providers and clinic staff evidence-based strategies to increase HPV vaccination uptake via training and educational resources. This program will be refined to provide tailored training and motivation to HIV providers and clinic staff to recommend and administer the HPV vaccine to HIV patients at the infectious disease clinic. Providers and clinic staff who are interested in participating will “enroll” online and complete an electronic informed consent before participating in the focus groups and completing the evaluation surveys. Providers and clinic staff are offered an opportunity to attend an in-service training that will provide education, training, and resources to help increase HPV vaccination at their clinic. Participation in the in-service will be offered to the entire clinic with opportunity for continuing education (CE) units to be earned. The in-service component is delivered under the purpose of quality improvement and does not require informed consent to attend.

Components of the in-service training consist of education and resources related to the 4 Pillars™ program, epidemiology of HPV-related cancers among HIV positive individuals, ACIP’s guidelines for HPV vaccination for immunosuppressed patients, safety profile of the vaccine, and the importance and effectiveness of delivering evidence-based recommendations for HPV vaccination. Providers and clinic staff who are within scope of practice to administer the HPV vaccine are asked to recommend and administer the HPV vaccine to eligible patients during each routine clinic visit. Consenting providers and clinic staff are asked to complete pre-intervention evaluations, an intervention evaluation every 3 months, and post-intervention evaluations via a secured link to complete online. Alternatively, paper copies will be provided to the providers and clinic staff and administered by an Immunization Champion to those who choose not to access the evaluations by email.

Each clinic site identifies an Immunization Champion (a medical assistant, nurse, or clinic manager) who will work and motivate the clinic staff and participate in biweekly updates of progress with the research coordinator. The Immunization Champion (IC) will encourage, remind, and ensure timely documentation of the HPV vaccination within the clinic’s electronic medical records and within GRITS. The IC helps maintain stock and storage of the vaccine and identify and address any issues with the vaccine inventory. The IC assists patients to complete Merck’s Patient Assistance Program to cover vaccination for those who are uninsured and qualify for the program. Lastly, the IC will contact patients on the monthly call list to schedule appointments or assist in reminders to patients to schedule the next visit for the follow up HPV vaccine.

Clinics receive a progress report that documents the clinic’s vaccination progress every three months. The research coordinator schedules group feedback sessions via in-person or webinar with the IC every three months to discuss: 1) the intervention evaluations completed by the providers and staff; 2) to learn of any barriers to HPV vaccination at the clinic; 3) brainstorm strategies to overcome the barriers; and 4) quality assurance of intervention fidelity.

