#### Statistical power

Based on our preliminary data, we found that HPV vaccination rate is around 13.5% (P0) in general, and another larger study in the literature found a very similar rate of 13.6% [10]. We powered the study to detect an uptake rate > 13.5% after the intervention. Thus, a sample size of 317 achieves 80% power to detect a superiority difference of 5% (PB-P0) using an exact one-sided test with a significance level (alpha) of 0.05. We anticipate a 5% superiority difference is reasonable to achieve with an uptake rate of 18.5% (PB) after the intervention. We will be able to reject the Null hypothesis and claim the uptake rate of > 13.5% after 54 patients have initiated the HPV test. After taking about 15% of the drop-off rate into account, we plan to include 365 participants among 3 clinics for the intervention phase. The calculation was by PASS 2020 for testing superiority of one proportion using the Exact test. The Null hypothesis is *P* < = 13.5% and the alternative hypothesis is *P* > 13.5%. For the control phase, we will query all eligible subjects from EMR database among the 3 clinics at 18 months pre-intervention, which could be approximately 2300 subjects [30]. Assuming we end up with the same number of subjects in both control (*N* = 317) and intervention phase (*N* = 317), we will have 81% statistical power to detect an HPV uptake rate difference of 9% (22.5% vs. 13.5%) by two-sided Fishers’ Exact Test and under significance level of 0.05. We anticipate such a difference would be feasible based on our best knowledge and the literature. Regarding the patient- level component of the intervention, all incoming eligible patients will be influenced, and hence 365 participants are the minimum number to capture the follow-up information, the actual number of sample size used for the calculation of HPV vaccination rate will be larger as the vaccination status will be captured automatically in EMR without a consent.

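### The plan does not settle whether the 365 consented participants or all eligible patients in the records carry the primary test; if the consented cohort does, its vaccination criterion can distort uptake in either direction

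*Protocol article*

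**What the plan says.** **Reach of the programme.** Under Clinic-level intervention approach, providers and staff within scope of practice "are asked to recommend and administer the HPV vaccine to eligible patients during each routine clinic visit". Nothing limits this to enrolled patients, and Statistical power confirms that "all incoming eligible patients will be influenced".

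**Enrolment.** The 365 participants consent individually. Under Clinic selection and patient eligibility, criterion 5 requires that they "have not received or completed the three dose HPV vaccine". Under Study outcomes, initiation means receipt of dose one or dose two.

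**Places that point to the consented cohort.**
- Methods/design opens by saying that rates are measured in the clinics and in those enrolled.
- Patient-level intervention approach makes the 365 consenting participants the intervention group.
- Statistical power derives 317 evaluable patients, says the trial can "claim the uptake rate of > 13.5% after 54 patients have initiated the HPV test", and adds: "After taking about 15% of the drop-off rate into account, we plan to include 365 participants among 3 clinics".

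**Places that point to all eligible patients.**
- Data analyses of primary outcomes estimates the rate from all eligible cases in both phases.
- The last sentence of Statistical power calls 365 the minimum needed for follow-up information. It expects the vaccination rate to rest on a larger number, because status comes from the medical records without consent.

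**The concern.** The programme acts on whole clinics from its launch, whereas the cohort forms patient by patient under a criterion that depends on the outcome itself. A patient who takes a first dose at a post-launch visit before being approached is a success of the programme. Whether that patient counts depends on two things the article leaves open: which set is tested, and whether criterion 5 excludes anyone with a dose or only those who have completed the series.

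The planned margin over the benchmark is only five percentage points, so a small shift in who enters the cohort changes the chance of success noticeably. A programme that works as planned could miss its target, or one with no effect could meet it. The success count is also tied to one denominator, so it cannot be carried over to the larger set named elsewhere in the plan.

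**Working it through.** **Inputs from Statistical power.** The benchmark is P0 = 13.5% ("we found that HPV vaccination rate is around 13.5% (P0) in general") and the target is PB = 18.5% ("reasonable to achieve with an uptake rate of 18.5% (PB) after the intervention"). The design uses N = 317 and a success count of 54, "using an exact one-sided test with a significance level (alpha) of 0.05".

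**Step 1: the plan's own figures.** The normal approximation gives n = [(1.645·√(0.135·0.865) + 0.842·√(0.185·0.815)) / 0.05]² = 316.05, rounded up to 317, as stated. With X the number of initiators, the exact binomial calculation gives:
- P(X ≥ 54 | 317, 0.135) = 0.0425, and P(X ≥ 53) = 0.0585, so 54 is the correct cut-off;
- P(X ≥ 54 | 317, 0.185) = 0.770.

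The starting point below is therefore 77.0%, not the stated 80%. That gap is a separate matter. For drop-off, 317 × 1.15 = 364.55, which gives 365. An allowance for drop-off fits participants who are followed up better than a rate read automatically from records.

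**Step 2: cohort tested, only patients without a dose enrol.** Assume 18.5% uptake among all eligible patients, a share f of those initiators vaccinated after launch but before being approached, and enrolees otherwise typical of the patients who remain. The article gives no value for f, so a range is shown.

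Cohort uptake = 0.185(1 − f) / (1 − 0.185f)

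| f (share of initiators) | Share of eligible patients, 0.185f | Cohort uptake | P(X ≥ 54 of 317) |
|---|---|---|---|
| 0% | 0% | 18.5% | 77.0% |
| 10% | 1.85% | 0.1665/0.9815 = 17.0% | 51.0% |
| 20% | 3.7% | 0.148/0.963 = 15.4% | 22.6% |
| 30% | 5.55% | 0.1295/0.9445 = 13.7% | 5.4% |

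Cohort uptake reaches the benchmark when the share of all eligible patients lost is (0.185 − 0.135)/(1 − 0.135) = 5.8%.

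**Step 3: cohort tested, patients with one or two doses may enrol and count as initiators.** Assume true new uptake equals the benchmark, 13.5%, and a share g of enrolees already has a dose. The share g is also an assumption.

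Observed rate = g + (1 − g)·0.135

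| g | Observed rate | P(X ≥ 54 of 317), a false success |
|---|---|---|
| 0% | 13.5% | 4.2% |
| 1% | 14.4% | 10.3% |
| 2% | 15.2% | 20.5% |
| 3% | 16.1% | 34.7% |
| 5% | 17.8% | 66.6% |

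**Step 4: all eligible patients in the records tested.** A patient vaccinated after launch but before approach stays in numerator and denominator, provided eligibility is judged at the start of exposure. The loss in Step 2 is then zero. The count of 54 no longer applies, however. With 365 patients the exact cut-off is 61. With 400 patients, 400 × 0.135 = 54 is simply the number expected under the null.

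**The case against.** The strongest reply is that the section on analysis of the primary outcome names all eligible cases, and the power section says the rate will use more than 365 patients taken from the records. On that reading nobody is lost, and much of the remedy is already planned. This stands, and it is why bias cannot be presented as a settled feature of the plan. It does not remove the contradiction. The only stated success rule, its drop-off allowance and two other sections still describe the consented cohort.

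A reader might go further and infer that the programme vaccinates all incoming patients, that only unvaccinated patients can enrol, and that the trial will therefore understate its effect. The article does not support this chain:
- Staff are asked to recommend and administer; the text does not say that every patient is vaccinated.
- Criterion 5 can also be read as excluding only patients who have completed the series.
- Participants watch the video before being seen at that visit, so a dose given then need not precede enrolment. The article does not say that this is the first post-launch visit.
- Consenting volunteers also receive education and reminders, which could raise their uptake.

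It is also fair to say that f and g are assumptions, and that an article may leave a per-patient index date to the full protocol. The absence of that date is not the finding. The date is needed only to make the chosen set work.

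**Conclusion.** The point holds as an inconsistency with a possible bias of unknown sign. The article names two different sets for the primary rate, and its success rule fits only one of them. If the consented cohort is used, criterion 5 can lower uptake (chance of success 77% falling to 51% or 23% when 10% or 20% of initiators are lost) or inflate it (false-success chance 10% to 67% when 1% to 5% of enrolees already have a dose). The two tables are separate illustrations under opposite readings of criterion 5; neither is a forecast. They rest on assumed shares and on enrolees being otherwise typical. If all eligible patients are counted from the start of exposure, the primary rate has no such loss. Mediator and moderator analyses that use participants' survey answers could still miss early responders. The plan should be corrected, because the change is cheap and removes a distortion that could decide the trial either way.

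**What to change.** 1. State in Methods/design, Patient-level intervention approach, Data analyses of primary outcomes and Statistical power that the primary rate and its test use all eligible patients in the electronic records and the state immunisation registry.
2. Restate the success count for the number actually analysed, for example as an exact-test rule instead of a fixed 54.
3. Set each patient's index date at the first clinic visit after programme launch. For the initiation endpoint, require no prior dose at that date, and count first doses from then on, including those given at or before consent.
4. Reword criterion 5 to say whether patients with one or two doses may join the survey cohort, and report the rate in the 365 consented participants as supportive.

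The cost is wording and analysis of records. The plan already foresees capture of vaccination status without consent, so no new data collection is needed.

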The Advancing HPV vaccination for HIV Positive Adults (CHAMPS) study seeks to expand the success of the 4 Pillars™ Program and tailor, refine, and implement in the HIV positive population, who are at high risk for HPV-related cancers and can obtain the most benefit from the vaccine. The strategies selected from the 4 Pillars™ Program are based on an extensive review of the HIV and related literature (Table 2) [21–28]. The intervention will be implemented in three HIV community clinics in Georgia, USA and enroll *n* = 365 PLWH, age 18–45 years, from those clinics. Guided by the RE-AIM framework, the proposed specific aims are:Tailor and refine the 4 Pillars™ program for implementation in three HIV community clinics in Georgia.Test the effectiveness of the 4 Pillars™ program as measured by an increase in uptake rate in initiation of the HPV vaccine (primary outcome) and vaccine completion (secondary outcome) compared to historical baseline vaccination rate (control) among PLWH. It is hypothesized after implementation of the 4 Pillars™ program, we estimate an uptake rate of > = 13.5% in initiation of HPV vaccination.Identify mediators and potential moderators (HPV knowledge and awareness and vaccine hesitancy) of the intervention effects on HPV vaccination.Assess the sustainability of the intervention in vaccine uptake post-intervention and assess scalability of the program for wider implementation via a future national randomized control trial.

**Table 2 Tab2:** Overview of selected intervention strategies guided by the 4 Pillars™ Program

Pillar Strategy	Level	Intervention Component
Pillar 1: Convenience	Provider-	• Incorporate recommendation of the HPV vaccine with each clinic visit. • Perform HPV vaccination on-site
Pillar 2: Communication and education	Patient-	• Provide patient education on risk of HPV-related cancer and benefit of HPV vaccination
Pillar 3: Enhanced systems	Clinic-	• Provider and staff education on HPV vaccination via an in-service training • Document vaccination in EMR system
Pillar 4: Motivation	Clinic- Provider- Patient-	• Clinic designated Immunization Champion to provide coaching and motivation of regularly tracked vaccination progress • Provide patient check-in, reminders, and motivation for HPV vaccine completion • Communicate vaccination reminders by text, phone, and social media messaging

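### Paper staff evaluations are administered by the Immunization Champion, who is part of the programme, so paper answers on implementation are open to social-desirability bias

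*Protocol article*

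**What the plan says.** The Clinic-level intervention approach section asks consenting providers and staff for pre-intervention evaluations, then "an intervention evaluation every 3 months, and post-intervention evaluations via a secured link to complete online". The next sentence offers paper copies as an alternative, "administered by an Immunization Champion to those who choose not to access the evaluations by email". Nothing limits the paper route to one of the three occasions, so it applies to all of them.

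The same section describes who the Champion is: "Each clinic site identifies an Immunization Champion (a medical assistant, nurse, or clinic manager) who will work and motivate the clinic staff". Table 2 in the Background lists the role as an intervention component under Pillar 4: "Clinic designated Immunization Champion to provide coaching and motivation of regularly tracked vaccination progress". The Champion also looks after vaccination documentation, vaccine stock and patient reminders.

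The research coordinator holds feedback sessions "with the IC every three months to discuss: 1) the intervention evaluations completed by the providers and staff". The fourth item on the agenda of those sessions is "quality assurance of intervention fidelity".

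Two later sections use the resulting data. Process evaluation takes frequency, duration, the extent of delivery as intended, attendance and cost from the intervention and post-intervention evaluations. Secondary aims summarises the evaluation and post-evaluation surveys to inform future scale-up.

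**The concern.** A person whose job is to motivate staff to carry out the programme is a poor choice to administer the form on which staff report whether it was carried out. A respondent who thinks delivery has been weak must say so on a form that comes from the colleague responsible for encouraging it. That colleague may be the clinic manager and will later take part in discussing the evaluations. The likely direction of any distortion is towards favourable answers.

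At stake are the implementation measures of the RE-AIM evaluation and the survey evidence on scalability. The fourth aim needs that evidence to support a future national randomised trial. Overstated implementation would make the programme look easier to deliver than it is. It would also confuse the reading of a disappointing uptake result, because poor delivery could be mistaken for an ineffective programme.

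The two response modes also differ in a way that matters for analysis. Online answers go through a secured link, while paper answers come by way of a programme insider. Pooling them without recording the mode leaves no means of seeing whether they differ.

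**Working it through.** The protocol gives no figure that depends on who administers the forms, so there is nothing to reproduce. The check is a comparison of what each section says.

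1. **Who administers which form.** Clinic-level intervention approach: the secured link is the default, and the Champion administers paper to those who do not use it. The exposure at the point of completion is therefore the paper subset only.
2. **Whether that person is part of what is evaluated.** Table 2 lists the Champion as a Pillar 4 component, and the clinic-level section adds documentation, stock and reminder duties. A measure of delivery as intended therefore includes, among other things, the Champion's own work.
3. **Whether there may be authority over respondents.** The role may be filled by a medical assistant, a nurse or a clinic manager. Only the last clearly implies seniority, so the risk differs by clinic and is greatest there.
4. **Whether the results return to that person.** Clinic-level intervention approach: yes, every three months, with no distinction between paper and online answers. The text does not say whether the answers are pooled or attributable.
5. **Which measures depend on the forms.** Process evaluation draws the extent of delivery, frequency, duration, attendance and cost from the evaluations. It draws involvement, acceptance, organisational spread and a second look at fidelity from post-evaluation interviews. No section says that the Champion conducts those interviews.
6. **Which measures do not depend on them.** Study outcomes takes initiation and completion from medical records and the registry. Process evaluation does the same for the month 24 to month 36 sustainability comparison.

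**Size.** Let *s* be the share of forms completed on paper and *d* the average upward shift in a rating caused by the Champion's involvement in the paper route. The pooled rating then rises by *s* × *d*. The documents give neither quantity. Since *s* lies between 0 and 1, the pooled shift lies between 0 (no one uses paper) and *d* (everyone does). Any single number would rest on invented values of *s* and *d*, so none is offered.

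**The case against.** The case on the other side has several parts.

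- **The default route avoids the Champion.** Anyone who wants distance can use the secured link. This stands, and it limits the point to the paper subset. It does not remove the point, because staff who choose paper may do so for reasons of access or habit.
- **Feedback with the Champion is deliberate.** The three-monthly sessions are a formative loop for finding barriers and improving delivery. This stands too, and the sessions should continue. They can work with pooled results.
- **A journal article leaves form handling to the full protocol.** This stands for envelopes, return routes and anonymity, and their absence is not the complaint. What the article does state is who administers the paper forms and who takes part in discussing the evaluations. That stated choice is what needs a safeguard.
- **The consequence is small.** It is: the forms feed descriptive process measures, interviews give a second source on fidelity, and a post-intervention focus group also informs scale-up.

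A reader might go further and infer that ratings of acceptance and fidelity as a whole are not independent of the person being rated. The documents do not support that. Nothing says that staff rate the Champion; Process evaluation describes the three-monthly form as concerned with vaccination progress, and the Champion is at most assessed indirectly as one component among several. Acceptance and involvement come from interviews. A reader might also infer that the Champion collects the completed forms, or can recognise individual answers because clinics have few staff. The text says neither, and it gives no staff numbers.

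**Conclusion.** The point holds in a limited form. A stated choice of data collector exposes paper answers about implementation to social-desirability bias, probably in the favourable direction, and most plausibly where the Champion is the clinic manager. It affects the measures that Process evaluation takes from the staff evaluations and the survey data that Secondary aims uses for scalability. It does not affect vaccine initiation, completion or sustainability, and the documents give no ground to extend it to the interview-based measures of involvement and acceptance.

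The conclusion assumes that at least some staff use paper and that being handed a form by a programme insider influences answers to some degree. Neither can be checked from the protocol, so the size of the effect is unknown. This is a minor improvement, worth making because it is cheap.

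**What to change.** In Clinic-level intervention approach, revise the sentence on paper copies so that completed forms go sealed and directly to the research coordinator, without passing through the Champion. State in the paragraph on feedback sessions that only pooled, de-identified evaluation results are discussed with the Champion. Record the response mode on every form, so that paper and online results can be set side by side before they are pooled. That comparison would be descriptive only, because staff choose their own mode and any difference may reflect who chooses paper.

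The cost is envelopes, a mode field and some extra handling by the research coordinator, who is already in place and has biweekly updates with each Champion. No endpoint, sample size or clinical procedure changes.
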